**Exclusion Criteria**
Failure to complete the run-in for dietary intake and physical activity; Unable/unwilling to give informed consent or communicate with local study staff; Inability to complete the study within the designated time frame because of plans to move out of the study area; Inability to attend the visits/appointments, evaluation measurements, and attend the intervention sessions at the FMH-UL; Schizophrenia, bipolar disorder, other psychotic disorders; Eating disorders; Major depression; Current consumption of more than 14 alcoholic drinks per week or other substance abuse, and/or current acute treatment or rehabilitation program for alcohol/substance abuse; Pregnancy/planning to get pregnant within the next 8 months; Having been pregnant within the past 6 months or breastfeeding; History of weight loss surgery or liposuction procedures; Current participation in a weight loss program; Losing >4.5 kg in the past three months; Current use of medications for weight loss; Thyroid disorders; Diabetes and cardiovascular disease; Other medical conditions known to affect energy balance homeostasis; Systemic corticosteroid treatment (weight gain associated with steroids may interfere with the intervention goals but use of hormone replacement therapy or oral contraceptives will not lead to exclusion).

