## Abstract

Preventive and educational programs directed to former elite athletes in the areas of healthy living are required. This is particularly relevant as obesity and health-related problems are observed in retired athletes, especially in those whose current levels of physical activity are below the recommendations. During their sports career, elite athletes are supported by a multidisciplinary team; upon retirement, no support is provided for the transition to a different lifestyle. So far, no program has been implemented to promote sustained healthy lifestyle behaviors in the post-career transition and evidence is lacking for such an intervention. Firstly, we aim to determine if Champ4life, a 1-year lifestyle intervention targeting inactive former athletes with overweight and obesity, is effective for reducing total and abdominal fat. Secondly, our purpose is to assess the effectiveness of the intervention on the levels of physical activity and sedentary behavior, resting energy expenditure, cardio-metabolic markers, physical fitness, energy balance components, eating self-regulation markers, and quality of life over 12 months. Champ4life is an evidence- and theory-based program using a randomized control trial design (intervention vs. control group) that will be conducted on 94 inactive former elite athletes with overweight and obesity. The first four months of the Champ4Life program include a nutritional appointment and 12 weekly, 90-min sessions. Classroom sessions seek to provide participants with key information and a toolbox of behavior change techniques to initiate and sustain long-term lifestyle changes. Participants will undergo baseline, 4-month, and 12-month measurements of body composition (primary outcomes), resting energy expenditure, physical fitness, metabolic markers, energy balance related-markers, and quality of life (secondary outcome). This trial will provide evidence on the effectiveness of the Champ4life program, a pioneer lifestyle intervention for retired athletes, offering tools for sustained changes in physical activity, sedentary behavior and diet, aiming to improve body composition and overall health-related markers.

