In this regard, interventions that support autonomous motivation for physical activity may foster increased engagement in self-regulation techniques and positively affect lifestyle health behaviors [35]. A systematic review on effective behavior change interventions designed to promote PA and healthy eating [36] clearly supported the inclusion of multiple self-regulatory techniques, specifically self-monitoring of behavior in combination with prompt intention formation, prompting specific goal setting, providing feedback on performance, and prompting review of behavioral goals [37]. Therefore, the inclusion of self-regulatory skills within autonomy-supportive educational sessions brings added value to encourage the adoption of energy balance behaviors.

This paper describes the protocol for a randomized controlled trial, which aims to evaluate the effectiveness of the Champ4Life program in supporting former athletes to improve their lifestyles versus a waiting list control group that is offered the program after the 1-year follow-up. The primary aim of the trial is to determine whether Champ4Life can help inactive former athletes aged 18–65 years with a body mass index (BMI) ≥25 kg/m^2^ to reduce total and abdominal fat mass over 12 months. Secondary outcomes include cardio-metabolic blood biomarkers (e.g., glucose, insulin, HbA1c, lipids, liver function), adaptive thermogenesis blood-derived indices (leptin and thyroid function), weight and waist circumference, improvement in other body components (fat-free mass, water compartments), resting systolic and diastolic blood pressure, physical fitness (e.g., cardiorespiratory fitness, strength), free-living PA, sedentary time, energy balance regulation, eating self-regulation markers, and quality of life.

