## 2. Methods

### 2.1. Study Design

Champ4life is a 1-year randomized controlled intervention program and will be performed among healthy former top-level athletes (i.e., having represented Portugal at least once in international sport championships, or been professional soccer players in the first divisions of the championships), with overweight and obesity. The intervention and all the measurements will take place at the Exercise and Health Laboratory in the Faculty of Human Kinetics, University of Lisbon (FMH-UL). A schematic description of the study phases is presented in Figure 1.

Before enrolling in the study, participants will perform baseline assessments of body composition, free-living PA, resting energy expenditure (REE), blood pressure, physical fitness, metabolic markers, eating self-regulation, energy balance components, and quality of life. All evaluations will be performed in three sessions, starting at 8:00 am in the morning after an overnight fast, with the exception of the physical fitness tests, physical activity monitoring, food recording and the quality of life questionnaire. A schematic description of all the measurements is presented in Table 1.

The study was approved by the Ethics Committee of the Faculty of Human Kinetics, University of Lisbon (Lisbon, Portugal) (CEFMH Approval Number: 16/2016) and will be conducted in accordance to the declaration of Helsinki for human studies from the World Medical Association [38]. It has been registered at www.clinicaltrials.gov (clinicaltrials.gov ID: NCT03031951) prior to participants’ recruitment.

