### 2.6. Waiting List (Control Group)

The control group will be placed on a waitlist to be offered the Champ4Life program after completing the 12-month follow-up measurements. In addition, this group will receive multimedia health information fortnightly by e-mail over the first 12-month period. The information provided will cover general healthy lifestyle topics, including tips for healthier dietary habits and to avoid excessive alcohol consumption and tobacco use.

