#### 3.1.2. Dual-Energy X-ray Absorptiometry

To estimate total and regional fat mass (FM) and fat-free mass (FFM), dual-energy X-ray absorptiometry (DXA; Hologic Explorer-W, Waltham, MA, USA) will be used. A whole-body scan will be performed and the attenuation of X-rays pulsed between 70 and 140 kV synchronously with the line frequency for each pixel of the scanned image will be measured. Total abdominal fat, which includes intra-abdominal fat plus subcutaneous fat, will be distinguished using DXA by identifying a specific region of interest (ROI) within the analysis program. Specific DXA ROIs for abdominal regional fat will be defined as follows: from ROI 1, the upper edge of the second lumbar vertebra (approximately 10 cm above the L4 to L5) to above the iliac crest and laterally encompasses the entire breadth of the abdomen, thus determining total abdominal fat mass [48].

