#### 3.3.7. Sample Size

For sample and power calculations, this study is powered on changes in total body fat assessed by DXA. We consider a type I error of 5% and a power of 80% (using the software GPower version 3.1.9.2) to detect an effect size of 0.58 for statistically significant differences in total body fat as reported elsewhere [78]. A total of 37 participants per group will be required. Considering a 20% drop out rate, as occurred in the selected study [78], we will enroll 94 participants (47 in each group).

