**Inclusion Criteria**
Former high-level athlete; Aged 18–65 years (male or female); Inactive (<20 min/day of vigorous physical activity intensity for at least 3 days per week or <30 min/day of moderate intensity physical activity for at least 5 days per week [39]); With overweight/obesity (BMI ≥25 kg/m^2^); Available to participate in the educational sessions at FMH-UL; Ready to modify their diet in order to lose body weight.

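### The pregnancy-planning exclusion looks 8 months ahead, but the primary fat outcome is measured up to 12 months, so a pregnancy planned for months 9–12 does not bar entry

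*Protocol article*

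**What the plan says.** The exclusion list in Table 2 names "Pregnancy/planning to get pregnant within the next 8 months". The same list also excludes women who were pregnant in the past 6 months or are breastfeeding. The inclusion list admits both sexes: "Aged 18–65 years (male or female").

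The follow-up is longer than the window. Section 2.1 states that "Champ4life is a 1-year randomized controlled intervention program". The Introduction gives the primary aim as helping participants to "reduce total and abdominal fat mass over 12 months". The Abstract sets the times: "Participants will undergo baseline, 4-month, and 12-month measurements of body composition (primary outcomes"). Section 3.1.2 names the instrument: "To estimate total and regional fat mass (FM) and fat-free mass (FFM), dual-energy X-ray absorptiometry" is to be used. Table 1 schedules DXA at all three moments, including the last (M3). Section 2.6 keeps controls on the waiting list and offers them the programme only "after completing the 12-month follow-up measurements", so both arms are followed for the full year.

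Section 2.2 says that exclusion criteria are checked with a yes/no question. Section 2.3 places all screening before randomisation.

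**The concern.** The article fixes two periods that do not match. The planning question looks 8 months ahead, while the primary outcome is read at 12 months. A woman who openly plans to conceive after month 8 answers no to the question as worded and is randomised. If her plan succeeds, her 12-month data may be affected: the M3 visits in Table 1 include DXA, bioimpedance, anthropometry, blood samples and a cardiorespiratory fitness test. Those results would either not be collected or would reflect the pregnancy as well as the intervention.

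The protocol already treats pregnancy as relevant to its measurements, since it bars current pregnancy, recent pregnancy and breastfeeding. At stake is a small number of primary outcomes that the woman's own answer at screening could have flagged.

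**Working it through.** **1. The two periods side by side.**

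| Item | Value | Source |
|---|---|---|
| Pregnancy-planning window | 8 months ahead | Table 2, exclusion criteria |
| Last primary-outcome measurement | 12 months | Abstract; Introduction; Table 1 (DXA at M3) |
| Study duration | 1 year | Section 2.1 |
| Eligible ages | 18–65, both sexes | Table 2, inclusion criteria |

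Uncovered time = 12 − 8 = 4 months, which is 4/12 or one third of follow-up, and it includes the 12-month time point. If the 8 months run from screening, the gap after randomisation is somewhat longer. The timed steps in Sections 2.2 and 2.3 are about one week each, so the addition is probably weeks, although flexible scheduling is allowed.

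**2. Whether another criterion closes the gap.** The criterion on completing the study in the designated time is tied to plans to move away. The criterion on inability to attend visits and evaluation measurements does not mention pregnancy, and a woman planning to conceive in month 10 may truthfully say that she can attend. Neither closes the gap.

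**3. How many women.** The article does not give the number of women. Section 4 expects more men than women. With assumed rates:

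- Women enrolled, assuming 20–40% of 94: 94 × 0.20 = 18.8 and 94 × 0.40 = 37.6, so about 19 to 38.
- Conceiving in months 9–12, assuming 2–5% of them: 18.8 × 0.02 = 0.4 and 37.6 × 0.05 = 1.9.

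That is about 0 to 2 participants. Both rates are assumptions, and the second is applied to all women up to age 65, so it is not a conservative choice.

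**4. Effect on power.** The plan's own figure comes first. Section 3.3.7 gives effect size 0.58, 5% type I error, 80% power, 37 per group, and 94 enrolled after 20% dropout. By the normal approximation, n = 2(z for alpha + z for power)² / d²:

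- One-sided 5%: 2 × (1.645 + 0.842)² / 0.58² = 36.8, so 37 per group.
- Two-sided 5%: 2 × (1.960 + 0.842)² / 0.58² = 46.7, so 47 per group.
- Dropout: 37 / 0.80 = 46.25, so 47 per group and 94 in total.

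The stated 37 is reproduced only with a one-sided test. Sidedness is not stated; that is a separate matter, so both versions are shown. Starting from 37 analysed per group, and removing further 12-month scans split evenly between arms, the exact t-test power is:

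| Further scans lost (assumed) | One-sided | Two-sided |
|---|---|---|
| 0 | 79.6% | 69.2% |
| 1 | 79.1% | 68.6% |
| 2 | 78.6% | 68.0% |
| 4 | 77.6% | 66.7% |

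At the assumed upper end of 2 scans, power falls by about 1 percentage point. Changing the window alters no sample-size figure.

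**The case against.** The strongest case on the other side is that the mismatch is real but hardly matters. On assumed rates it touches 0 to 2 people, and the 20% dropout allowance could absorb that. Randomisation is stratified by sex (Section 2.4), so women should be split about evenly between arms, and nothing suggests that losses would differ by arm. A woman who conceives after month 8 would be at most about four months pregnant at month 12, and the article does not say how much that would shift fat mass. A woman who expects to miss the final measurements could be excluded under the attendance criterion. All of this stands as to size. It does not remove the conflict between two stated figures, nor does it explain the 8 months.

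Three stronger readings are tempting, and the document does not support them.

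- A reader might infer that the plan exposes a pregnancy to an X-ray scan. No section says that a participant known to be pregnant would be scanned. Checks before DXA and the handling of pregnancy in follow-up are details that an article commonly leaves to the full protocol. A question about plans would not prevent unplanned pregnancies at any window length either.
- A reader might infer that the criterion fails in its purpose. The article does not state that purpose. The criterion excludes current pregnancy, and its window covers the group sessions of about four months (Section 2.5) and the 4-month measurement. The defect is partial cover of follow-up.
- A reader might infer that the 12-month results of the trial as a whole become uninterpretable. The figures above point to one or two individuals at most.

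**Conclusion.** The point holds as an inconsistency between a stated eligibility figure and the stated measurement schedule. The planning window ends at least 4 months before the last primary-outcome measurement, so a woman who declares a plan for months 9–12 is eligible, and her 12-month fat mass, weight and metabolic outcomes could foreseeably be missing or distorted. This rests on the text alone and is firm.

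The size is not firm. The number affected cannot be derived from the document; 0 to 2 of 94 depends on assumed proportions of women and of conceptions. On that range the loss of power is negligible. The reason to act is that the problem is foreseeable at screening and nearly free to avoid. No large threat to the primary analysis and no safety failing is claimed.

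**What to change.** Reconcile the pregnancy-planning window in Table 2 with the 12-month measurement schedule, so that it covers the period to the last primary-outcome measurement, and align the yes/no screening question with it. It would help to say from which date the window is counted, because screening precedes randomisation. If 8 months was deliberate, state the reason instead.

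The cost is one figure in the table and the matching line on the screening form, plus a very small loss of eligible women. The sample size, the measurement schedule and the analysis do not change.
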